**Figure 2 F2:**
[figure not shown]
Schedule of enrolment, interventions and assessments. t1 = −2(−1) weeks, 0 = baseline, t1 = week 1, t2 = week 16, t3 = end of treatment week 24, t4 = follow-up week 28.

### Intervention group

2.12

Participants in the intervention group will have 24 weeks of Baduanjin exercise training (Fig. 3). At the same time, they will also receive regular medical or rehabilitation treatment and health training. The included patients will receive movement guidance from the teacher of Baduanjin of Fujian university of traditional Chinese medicine before the exercise training of Baduanjin, and begin the exercise training intervention of Baduanjin after they recognize the patient's movement. Baduanjin exercise training will last 24 weeks, 3 days a week, 40 minutes a day. The cultivation plan of Baduanjin comes from the Health Qigong Management Center of General Administration of Sport of China: Health Qigong-Baduanjin (2003).^[32]^ The whole exercise of Baduanjin 26 consists of 10 movements (including the preparatory movement and the finishing movement) (Fig. 3).

**Figure 3 F3:**
[figure not shown]
Baduanjin exercise training diagram. (A) Starting form. (B) The first form. (C) The second form. (D) The third form. (E) The fourth form. (F) The fifth form. (G) The sixth form. (H) The seventh form. (I) The eighth form.

### Control group

2.13

Participants in the control group did not receive any special sports training. These participants will be required to maintain their original lifestyle.

### Follow up

2.14

After 24 weeks, all participants were expected to enter another 4-week follow-up period. At a later stage, participants will return to their original lifestyle. The research assistant will conduct a telephone follow-up or home visit every Monday morning. Information about participants’ subjective feelings, medication, and daily activities will be recorded. Primary and secondary outcomes will be assessed at the end of the follow-up period.

### Participant retention and persistence

2.15

The success of the intervention depends to a large extent on the dynamic participation of participants. In order to stimulate the active participation of participants, the staff will adopt several strategies to improve the compliance of the intervention plan:

(1) After the participants are randomly assigned to the intervention group, the researcher will elaborate on the benefits of the Baduanjin;

(2) Professional teachers will guide the patients to carry out Baduanjin training, which will stimulate the participation of patients;

(3) The research assistant reminded the subjects to carry out the Baduanjin exercise according to the wechat group's learning plan and complete the Baduanjin training under the supervision of professional teachers.

The attendance rate of Baduanjin training will be evaluated by recording the training days. Patients who do not attend the training course will be considered as absenteeism.

In order to improve the retention rate of participants, subjects will be randomly assigned, and the research assistant will make every effort to ensure that the subjects remain normal throughout the study period.

It includes the following ways:

(1)the assistant researcher will maintain the participation of participants through interviews and telephone calls;(2)Communicate regularly through materials, dialogues, and other means to inform the participants of our support;(3)Flexible arrangement of learning time and the resolution of a time conflict.

### Outcome indicators

2.16

#### 
Primary endpoint

2.16.1

The main outcome of our study will be the change in VAS score of pain from baseline to the completion of the intervention (week 24).^[30]^ Patients will quantify pain intensity by marking the most relevant points anchored by 2 descriptors on a 100 mm horizontal line: 100 for ”most imaginable pain” and 0 for ”no pain”.

#### 
Secondary ending

2.16.2

Pain-related disability index is used to measure general disability related to pain.

The Pain Disability Index is a widely used and researched tool for measuring pain-related disability, especially in chronic low back pain, fibromyalgia, cancer, or chronic generalized pain.^[33]^ Pain Disability Index is mainly composed of 7 projects, including family responsibilities, entertainment, social activities, occupation, sexual behavior, self-care, and life support activities. Each item is evaluated using a numerical score scale of 0 to 10, where 0 means no disability, 10 means the highest disability, and the total score is 70 points. The higher the score, the more the pain interferes with daily activities. Pain Disability Index is easy to understand and is an effective and reliable tool.

The Quebec back pain disability scale is used to measure disability related to specific back pain.^[34]^

The Quebec back pain disability scale is mainly used to assess the difficulty of various daily activities patients with low back pain. These activities are mainly divided into 6 areas, across a total of 20 questions: bed rest (question 1–3), sitting (question 4–6), walking (question 7–9), exercise (question 10–12), bending over (question 13–16) and carrying heavy objects (questions 17–20). Each question has 6 options, with a score of 0 to 5. A score of 0 means no difficulty, a score of 5 means unable to complete, and a higher score means more severe dysfunction. The total score is 100 points.

Measure the health-related quality of life through the SF-36 Health Survey.^[35]^

Health-related quality of life is evaluated using SF-36, which is a routine health questionnaire. The scale has 36 items divided into 8 dimensions: physical function, physical function, physical pain, general health, energy, social function, emotional function, and mental health. The first 4 dimensions belong to the field of physiology, while the last 4 dimensions belong to the field of psychology. The conversion ratio score of each field and each dimension of SF-36 is 0–100 minutes; the higher the score, the better the Health-related quality of life.

Roland Morris Disability Questionnaire (RMDQ), which has 24 items, from the affect overview disease (Sickness Impact Profile) simplifies RMDQ.^[36]^ It chooses 24 foods closely related to lower back pain. RMDQ is used to assess the condition of patients with low back pain within 24 hours before the test. These include walking, standing, bending, bed rest, clothes, sleep, self-care, and daily activities such as 8 aspects. The answer to each question is “yes” (1 point) or “no” (0 points). The total score is 0 to 24 points; the higher the score, the more severe the dysfunction. Some researchers believe that RMDQ has good reliability and effectiveness in assessing short-term changes before and after treatment for low back pain.

Global Perceived Effect is used (-5 to +5) to measure the overall perceived therapeutic effect.^[37]^

Overall Perceived Effect: This is the patient's subjective perception of the degree of pain, which is more used for the patient's perception of pain changes. Overall Perceived Effect is a 7-point system with the following specific regulations: 1 point: more damage than before; 2 points, more painful than before; 3 points, a little less damage than before; 4 points, no change; 5 points, pain is slightly improved; 6 points, pain improvement is more obvious; 7 points, almost no pain.

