**Methods::**

This randomized, controlled, evaluator-blind, two-arm, parallel clinical trial will include 90 outpatients with chronic low back pain recruited from the First Hospital of Nanping City, Fujian Province. The patients were randomly assigned to the intervention group (Baduanjin exercise training) and the control group (not receiving any special exercise training) at a ratio of 1:1. Patients in the intervention group will receive Baduanjin exercise training 3 times a week for 24 weeks. The 2 groups received a 4- week follow-up observation at 24 weeks. The main result from the intervention before intervention to 24 weeks later, and the follow-up of 4 changes the visual analog scale score at weeks, and by independent t are tested groups. It will also review the Pain-related disability index, The Quebec Back Pain Disability Scale, Health-related quality of life, Roland Morris (Roland Morris) Disability Questionnaire, Overall Perceived Effect (OPE) and safety Compare. Cost data for cost-benefit and cost-benefit analysis will be collected.

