### Research design

2.2

This study is a randomized, controlled clinical trials, will conform to the conditions of 90 participants according to the proportion of 1:1 were randomly divided into intervention group (Baduanjin group) and control group (not exercise training group). All the members of the intervention group received Baduanjin training 3 times a week for 24 weeks. All cases in the control group did not receive any exercise training for 24 weeks. Primary and secondary outcomes will be measured at baseline, 8, 16 and 24 weeks after intervention, and the next 4 weeks. The research design flowchart is shown (Fig. 1). The research protocol was described in accordance with “ SPIRIT 2013 statement: defining standard protocol items for clinical trials ”.^[29]^

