### Statistics

2.21

All data are statistically analyzed using Statistical Product and Service Solutions (SPSS©), version 20.0 (IBM Corp., Armonk, NY, USA). Continuous variables will be mapped by the mean and its SE (normal distribution) or median and IQR (non-normal distribution). Categorical variables will be delineated as a frequency or percentage. The baseline characteristics between the comparison groups will be compared using the *t* -test or Mann-Whitney *U* test for continuous variables, while Pearson χ^2^ or Fisher exact test will be employed to compare categorical variables. The analysis of primary or secondary results will be established with the intent to treat principle, and missing data will be interpolated using multiple imputation methods. Student's *t* test or Mann-Whitney *U* test will be used to analyze the difference between the intervention group and the control group at each time period (8 weeks after the intervention, 16 weeks, and 24 weeks or 4 weeks of follow-up). In the safety analysis, the total adverse event rate and adverse event rate associated with Baduanjin were tested by Pearson χ^2^ or Fisher's exact test.

Primary analysis: treatment efficacy. The statistical analysis of primary and secondary results will be based on treatment principles. The effect of the intervention on pain distress, pain intensity, function, disability, and overall sensory effects will be determined using a linear mixed model (random intercept and fixed coefficient), which includes treatment, time, and time interaction. The treatment coefficient of time interaction provides an estimate of the effect of Baduanjin intervention. The magnitude of the treatment effect will be calculated for each follow-up time point. If there is a statistically significant treatment effect at any point in time, we will also calculate the number of treatments (NNT) required to achieve pain recovery.

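### The perceived-effect outcome has two incompatible ranges and an out-of-order category, and its treatment-by-time coefficient alone is not a valid effect estimate

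*Protocol article*

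**What the plan says.** Section 2.16.2 introduces the outcome with "Global Perceived Effect is used (-5 to +5) to measure the overall perceived therapeutic effect". The paragraph that follows changes both name and range: "Overall Perceived Effect is a 7-point system with the following specific regulations", with scores from 1 to 7. The middle of that list reads "3 points, a little less damage than before; 4 points, no change; 5 points, pain is slightly improved". The construct is also described loosely: "This is the patient's subjective perception of the degree of pain, which is more used for the patient's perception of pain changes". The abstract lists a single outcome of this kind, "Overall Perceived Effect (OPE) and safety Compare".

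Section 2.2 sets the schedule for all outcomes without exception: "Primary and secondary outcomes will be measured at baseline, 8, 16 and 24 weeks after intervention", and again 4 weeks later.

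Section 2.21 puts an overall perceived outcome (most naturally this one) into a linear mixed model with a random intercept and terms for treatment, time and their interaction. It adds: "The treatment coefficient of time interaction provides an estimate of the effect of Baduanjin intervention". The same section also plans an effect size at each follow-up time, and a t-test or Mann-Whitney U test between arms at weeks 8, 16 and 24 and at follow-up.

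**The concern.** Three things need settling before this outcome can be read.

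1. **Range.** A scale from -5 to +5 and a scale from 1 to 7 cannot be the same instrument. A reported mean or difference has no fixed meaning until one is chosen.
2. **Order.** If score 3 means slightly better, a higher score is not always a better one. Means and ranks both assume that it is.
3. **Effect measure.** A rating of change relative to an earlier state has nothing to measure before treatment. The interaction coefficient takes its meaning from a reference visit, and here that reference is either absent or without content.

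At stake is the interpretation of one secondary outcome, including any comparison with other trials that use a perceived-effect scale.

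**Working it through.** **Ranges side by side.** In whole points, -5 to +5 has 11 steps centred on 0; 1 to 7 has 7 steps centred on 4. The linear map between them is y = 4 + (3/5)x. It sends -5, 0 and +5 to 1, 4 and 7, but +1, +2, +3 and +4 to 4.6, 5.2, 5.8 and 6.4. Only the ends and the midpoint correspond, and one point on the first scale is 0.6 of a point on the second.

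**Order of the labels.** Reading the 7-point list as printed:

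| Score | Direction of the label |
|---|---|
| 1, 2 | worse |
| 3 | slightly better |
| 4 | unchanged |
| 5 | slightly better |
| 6, 7 | better |

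Two categories describe slight improvement, on opposite sides of unchanged, and none describes slight worsening. If slightly improved patients split equally between 3 and 5, their mean is (3 + 5)/2 = 4, the score for unchanged.

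**What the interaction estimates.** Let d(t) be the arm difference at visit t. With time as visits, the coefficient for week 24 is d(24) minus d(reference).

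- No baseline score, so week 8 is the reference, and a steady 1-point benefit: 1 - 1 = 0. The benefit falls into the treatment main effect. A linear time term gives the same answer, because a constant d(t) has slope 0.
- Baseline set to unchanged for everyone: 1 - 0 = 1. The interaction then carries the effect, but only through an imposed constant.

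**Size.** The article gives no figure for this outcome. Its sample size, for VAS, supplies the numbers per arm. Pooled SD = sqrt((1.7² + 1.39²)/2) = 1.553 and the difference is 3.70 - 2.37 = 1.33. Then n = 2(1.960 + 1.645)²(1.553/1.33)² = 35.4, so 36, and 36/0.80 = 45 per arm, as stated in section 2.7.

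The simulation used 36 and 45 per arm and 2,000 runs per scenario. It compared the group-by-time F test of a random-intercept model with a t-test at week 24, both at 0.05. Assumed, not in the document: SD 1.5, within-patient correlation 0.5, 1-point benefit at week 24. Rejection rates for 36 / 45 per arm:

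| Benefit at weeks 8, 16, 24, 28 | Interaction, no baseline | Interaction, baseline fixed at unchanged | Week-24 t-test |
|---|---|---|---|
| 1, 1, 1, 1 | 5.3% / 5.5% | 82% / 91% | 80% / 89% |
| 0.5, 0.75, 1, 1 | 24% / 30% | 75% / 86% | 81% / 90% |
| 0.25, 0.5, 1, 0.8 | 47% / 55% | 72% / 84% | 79% / 88% |
| 0, 0.5, 1, 1 | 80% / 88% | 90% / 96% | 80% / 88% |

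The week-24 column comes from the no-baseline runs; over all runs that test rejects in 78 to 90%. A second setting (steady 0.6 SD benefit, correlation 0.6, 36 per arm, 4,000 runs) compared a t-test on week 24 minus week 8 with a t-test at week 24 and gave 5% against 71%. The power figures move with the assumptions. The 5% does not: it is the type I error rate, because the quantity tested is zero.

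**The case against.** A reader might infer that the planned analysis cannot detect an effect on this outcome, or that an early benefit would be reported as none. The document does not support that. Section 2.21 also plans an effect size and a two-group test, including a rank test, at every follow-up time, so a benefit at week 8 or week 24 would be tested directly. The 5% figure needs both the absence of a baseline score and a perfectly steady benefit. Section 2.2 schedules a baseline, and a 24-week exercise course could plausibly give a growing benefit. This objection stands, and it limits the analysis point to the interaction coefficient taken alone.

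It does not rescue that coefficient. The 82 to 91% obtained with a baseline comes from fixing every patient at unchanged, which is not a measurement.

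The second objection is that score 3 is a slip in the English text. Scores 1 and 2 are worse and 5 to 7 better, so the intended direction of 3 can be guessed, and the same section has other language slips. That is likely, but the label as printed is still wrong. A reader might also infer that patients have already been scored on mixed scales or miscoded. The case report form is not shown, so this cannot be said. It can only be checked.

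**Conclusion.** The two ranges contradict each other and score 3 is out of order. Both follow from the text alone, without assumptions, and either one leaves the score undefined as written. Whether the order error reaches the data depends on the wording of the form.

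On the analysis, the supportable conclusion is narrow. The outcome has no meaningful baseline, so the treatment-by-time coefficient alone is not a valid measure of its effect. With no baseline score, its rejection rate for a 1-point week-24 benefit runs from about 5% (steady benefit) to 88% (benefit starting after week 8), under the assumed SD and correlation. The per-visit comparisons already planned would still detect such a benefit.

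This should be corrected, but it concerns one secondary outcome. The VAS primary outcome and the 45 per arm are untouched.

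**What to change.** - In section 2.16.2, name the one instrument and range printed on the case report form and delete the other.
- If the 7-point form is used, correct category 3 so that all the labels run in order. Compare the article with the form patients actually complete. If the form carries the faulty wording, flag the answers collected under it.
- In section 2.2, exempt this outcome from the baseline assessment.
- In section 2.21, state that its effect is the between-arm difference at week 24, taken as a model contrast or from the rank test already planned, and not the interaction coefficient.

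The cost is a text edit and possibly one form correction. Section 2.6 says the trial began in October 2020 and section 2.20 says data are collected on paper, so the form check should come first. No change to the sample size or the primary analysis is needed.

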### Economic analysis

2.17

Cost-effectiveness studies will be conducted simultaneously. Cost data will be collected using a separate economic analysis case report form. Medical expenses will include official medical expenses (paid by patients to the hospital) and unofficial medical expenses, including non-prescription drugs, health food, medical equipment and other required expenses. Non-medical costs include transportation costs, care costs and time costs. Loss of work efficiency will also be assessed.

### Assess safety

2.18

Each examination will be a physical examination, and vital signs and adverse events will be checked. To check the safety of Baduanjin, blood pressure, heart rate, blood tests and nervous system checks will be performed during the first and fourth data collection. Any adverse events during the clinical trial will be documented and evaluated in the case report form. The incidence of adverse events will be calculated. Adverse events associated with the intervention will be monitored and appropriately addressed.

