### Study schedule

2.11

The research schedule is listed (Fig. 2). The trial will include a screening phase, an intervention phase and a follow-up phase. During the screening phase, participants sign informed consent. Researchers will obtain basic demographic information and use VAS to determine whether participants are eligible for clinical trials. If participants are undergoing rehabilitation training or exercise therapy, we will implement a 2-week flushing period. During the 24- week treatment period, the 2 groups of patients were measured before the intervention, at 8, 16, and 24 weeks after the last training session of the week. In the intervention group, Baduanjin training was performed 3 times a week. The follow-up survey of the intervention group will be conducted 4 weeks after the last training, and the control group will be conducted at the 28th week.

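### The between-arm test of the total adverse event rate is at risk of unequal ascertainment: any event in the trial counts, but only the Baduanjin arm has up to 72 teacher-supervised sessions during treatment

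*Protocol article*

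**What the plan says.** **What is counted.** Section 2.18 provides for an adverse event check at each examination. It then adds: "Any adverse events during the clinical trial will be documented and evaluated in the case report form. The incidence of adverse events will be calculated". Nothing limits the count to events found at examinations.

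**What is tested.** Under section 2.21, "the total adverse event rate and adverse event rate associated with Baduanjin were tested by Pearson χ^2^ or Fisher's exact test".

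**Contact in the Baduanjin arm.** Section 2.12: "Baduanjin exercise training will last 24 weeks, 3 days a week, 40 minutes a day". Section 2.15 has reminders sent through a WeChat group and participants who "complete the Baduanjin training under the supervision of professional teachers".

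**Contact in the control arm.** Section 2.13 gives controls no special training: "These participants will be required to maintain their original lifestyle".

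**Contact common to both arms.** Section 2.11: "the 2 groups of patients were measured before the intervention, at 8, 16, and 24 weeks after the last training session of the week". The follow-up survey comes four weeks after the last training in the Baduanjin arm, and for the other arm, "the control group will be conducted at the 28th week". In the four-week follow-up period (section 2.14), "The research assistant will conduct a telephone follow-up or home visit every Monday morning". Section 2.15 also mentions retention interviews and telephone calls, not limited to one arm and without a stated frequency.

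**Blinding.** Section 2.9 leaves participants and physicians unblinded. Evaluators and statisticians are blinded.

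**The concern.** The document itself fixes three elements: frequent supervised contact in one arm only, open-ended recording of events, and a significance test on the resulting total. Together they leave the test open to detection bias. A brief event such as soreness, a pain flare or dizziness during a supervised session happens in front of a teacher working within the trial. The same event in a control may wait up to eight weeks for the next scheduled examination and has to be remembered until then. Unblinded participants may add to the difference.

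Safety is part of the main objective (section 2.1), and the Discussion presents the safety evaluation as a first. If more events are recorded in the Baduanjin arm, the reader cannot tell harm from closer observation. A false safety signal could result, or a real difference could be dismissed as a reporting artefact. The point concerns the total event rate, not the test of Baduanjin-related events.

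**Working it through.** The plan gives no figure for the adverse event comparison, so there is none to reproduce. The check has two parts.

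**1. Contact opportunities**

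| | Baduanjin arm | Control arm |
|---|---|---|
| Supervised sessions, 24 weeks (2.12, 2.15) | 3 × 24 = 72 at most | 0 |
| Scheduled post-baseline examinations during treatment (2.11) | 3 (weeks 8, 16, 24) | 3 (weeks 8, 16, 24) |
| Scheduled total during treatment | 72 + 3 = 75 at most | 3 |
| Retention interviews and calls (2.15) | number not stated | number not stated |
| Monday contacts in the 4-week follow-up (2.14) | about 4 | about 4 |
| Assessment at end of follow-up (2.11) | 1 | 1 |

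The imbalance is confined to the treatment period, which is also the period of exposure to the exercise.

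**2. What unequal capture could do to the test**

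Inputs:
- 45 per arm (section 2.7).
- Two-sided 5% level; Fisher's exact test or Pearson χ² without continuity correction (tests from section 2.21; two-sidedness and no correction assumed).
- Assumed, because the document gives neither: the true proportion π with at least one event, equal in both arms, and the probabilities c_B and c_C that such a patient is recorded as having an event.

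Recorded proportions are p_B = π·c_B and p_C = π·c_C. The false-significance rate is the exact sum over all pairs (a, b) of patients with events:

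P = Σ Bin(a; 45, p_B) · Bin(b; 45, p_C) · 1[test p-value < 0.05]

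| True π | Capture, Baduanjin v control | Recorded proportions | Fisher | Pearson |
|---|---|---|---|---|
| 30% | 100% v 100% (reference) | 30% v 30% | 3.0% | 5.3% |
| 30% | 90% v 80% | 27% v 24% | 3.6% | 6.6% |
| 30% | 90% v 70% | 27% v 21% | 6.2% | 10.8% |
| 30% | 90% v 50% | 27% v 15% | 20.3% | 30.0% |
| 40% | 90% v 50% | 36% v 20% | 31.0% | 40.7% |
| 10% | 90% v 50% | 9% v 5% | 3.8% | 12.7% |

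For example, 0.30 × 0.90 = 0.27 and 0.30 × 0.50 = 0.15.

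Mild differential capture hardly moves the error rate. A large difference in capture of common events raises it several-fold. With rare events Fisher's test stays below 5%, because it is conservative at small counts, while Pearson's does not.

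**The case against.** **Sessions are not named as a place where events are collected.** This stands. Section 2.15 speaks only of recording attendance, and section 2.18 ties the scheduled check to examinations that are the same in both arms. That events come to light at sessions is an inference. But section 2.18 also has any event during the trial documented, and nothing excludes one seen or mentioned at a session.

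**Control contact is more than three visits.** This also stands for the trial as a whole. There is a week 28 assessment, about four Monday contacts and the retention calls, and section 2.10 allows conventional care if needed and gives both arms the same health education. The Monday contacts and the week 28 assessment come after the exposure and are common to both arms. Nothing shows that the retention calls, which are not specific to controls, offset the 72 sessions.

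**The size is assumed.** Correct. The larger figures need both a common event and a wide gap in capture.

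**An article may leave collection details to the full protocol.** True of the wording of questions and of form fields, and their absence is not the point. The article itself states the contact schedule, the open recording rule and the test.

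**Leaving session-reported events out of the comparison could hide real harm.** This stands. An exercise-induced event may be forgotten by the next visit, up to eight weeks later. All recorded events must therefore still be reported by arm.

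**Conclusion.** The point holds as a risk. With recording open to any event, unblinded participants and far more study contact in one arm during treatment, the test of the total adverse event rate in section 2.21 is at risk of unequal ascertainment, probably towards more recorded events in the Baduanjin arm.

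A reader might go further and infer that the comparison is confounded, or that controls are seen only three times. The document supports neither. It does not say that events are collected at sessions, the scheduled check is symmetric, and three is the number of scheduled post-baseline examinations within the 24 weeks, not of all contacts.

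Nor can the size be stated. Over the assumed cases at a 30% true proportion, false significance runs from about 4% (Fisher) and 7% (Pearson) to 20% and 30%. It is higher if events are more common. At a 10% true proportion it is about 4% and 13%, even with 90% v 50% capture. These figures are illustrations and rest on equal true proportions and the capture probabilities shown.

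**What to change.** In sections 2.18 and 2.21:

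1. Base the between-arm test of the total adverse event rate on events elicited by one standard question with the same recall period, put by the blinded evaluator at weeks 8, 16, 24 and 28 in both arms.
2. Record the source of each report (examination, training session, telephone call or home visit, other).
3. Continue to record every event. Report all recorded events by arm descriptively beside the formal test, with session-reported events shown separately.

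The cost is one question on the existing visit form and one source field. No extra visit is needed and clinical care does not change. The downside is that some minor events reported only at sessions leave the formal test, although they remain in the reported totals and in the listing.
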